## Abstract

**Background:**

There is a lack of psychotherapeutic trials of treatments of comorbid depression in cancer patients. Our study determines the efficacy of a manualized short-term psychodynamic psychotherapy and predictors of outcome by personality and quality of the therapeutic relationship.

**Methods/design:**

Eligible breast cancer patients with comorbid depression are assigned to short-term psychodynamic psychotherapy (up to 20 + 5 sessions) or to treatment as usual (augmented by recommendation for counseling center and physician information). We plan to recruit a total of 180 patients (90 per arm) in two centers. Assessments are conducted pretreatment, after 6 (treatment termination) and 12 months (follow-up). The primary outcome measures are reduction of the depression score in the Hospital Anxiety and Depression Scale and remission of depression as assessed by means of the Structured Clinical Interview for DSM IV Disorders by independent, blinded assessors at treatment termination. Secondary outcomes refer to quality of life.

**Discussion:**

We investigate the efficacy of short-term psychodynamic psychotherapy in acute care and we aim to identify predictors for acceptance and success of treatment.

**Trial registration:**

ISRCTN96793588

## Background

Breast cancer is associated with multiple losses (e.g. regarding body image, sexuality, social relationships), strains (e.g. pain, fatigue) and threat to life. Depressive disorders are the most frequent mental comorbidities. The combined prevalence of major, minor depression and dysthymia in cancer patients was estimated at 22%
[1,2]. In clinical routine, however, depression often escapes medical attention
[3,4]. Without adequate treatment, depressive disorders in medically ill lead to substantial decrements of quality of life
[5], longer inpatient treatment, prolonged work disability and inadequate illness behavior (e.g. lack of compliance) and even higher mortality
[6].

Recently, there has been positive - somewhat limited - evidence for the effectiveness of pharmacological and psychotherapeutic treatments with randomized controlled trials (RCT’s) for depressed cancer patients, e.g. of cognitive behavior and problem-solving therapy for recently diagnosed, mildly to moderately depressed patients and of supportive-expressive group therapy for patients with advanced disease. Studies often suffer from methodological problems, such as selected or small samples, unclear or missing randomization, no manualization or control on treatment adherence. Unfortunately, only a minority of the trials has adequately assessed depression. A recent study ascertained clear preferences of cancer patients regarding speaking about their concerns and fears rather than accepting psychopharmacological treatment
[7].

There has been increasing evidence supporting individual supportive-expressive psychotherapy as an effective short-term psychodynamic psychotherapy (STPP) for various mental disorders such as depression
[8], generalized anxiety
[9] and social phobia
[10]. Based on the experience of developing a German manual
[11] and training therapists in a multicenter RCT by two authors ([name], AH), a specific treatment manual was developed for treating depression in breast cancer patients
[12]. We assumed that psychodynamic treatment is suitable to deal with the intrapsychic and interpersonal conflicts generated by the experience of cancer. We also assumed that maladaptive interpersonal relationship patterns play a pivotal role in this context and that therapeutic changes of these patterns lead to remission or improvement of depression. Also, the combination of interpretative and supportive treatments renders supportive-expressive psychotherapy flexible to deal with crises in the course of a potentially life-threatening disease.

There is still a lack of knowledge on predictors of outcome of psychotherapy. Blatt & Zuroff
[13] found that the success of short-term outpatient treatment depended mostly on two factors: the quality of the therapeutic relationship and patients’ pretreatment personality. In particular, those patients who were perfectionistic or self-critical before treatment improved less than those with low perfectionism. They obviously found it difficult to relate to their therapists in the time-limited treatment of depression. Thus, an additional issue of our trial is to determine the effects of personality and quality of the therapeutic relationship on treatment outcome.

## Methods/design

In a multicenter trial, patients are recruited in the centers of Mainz and Leipzig in close cooperation with gynecological and oncological centers in the respective regions (list of cooperating clinics cf. appendix). Assessments are done by independent, trained and supervised research-assistants, who are blind to the intervention. Quality assurance is performed by the independent Interdisciplinary Center for Clinical Trials with regular monitoring visits including source data verification of all randomized patients, control of patient existence and written consent of all screened patients. Monitoring is defined in a monitoring manual and all results of the monitoring are written down in monitor reports.

### Participants

Members of the oncological teams report eligible consecutive patients to trained research assistants. Following detailed information those who provide written consent with study participation are entered into the study and fill out the screening questionnaire. Patients are required to fulfill the test criteria on the Hospital Anxiety and Depression Scale (HADS, depression score ≥8) and a diagnosis of a depressive disorder by the Structured Clinical Interview for DSM IV Disorders (SCID-I). Patients are randomized to the intervention or control group only if a diagnosis of a depressive disorder is made based on the aforementioned criteria. Inclusion and exclusion criteria are listed in Table
1.

**Table 1 T1:** Inclusion and exclusion criteria

*Inclusion criteria:*	· Diagnosis of breast cancer
	· Curative treatment
	· German language
	· Age 18-70
	· Depression score (HADS ≥ 8)
	· Depressive disorder according to SCID-I (ICD-10 diagnoses: depressive episode F32.-, recurrent depressive episode F33.-; Dysthymia F34.1, adjustment disorder F43.21)
	· Written consent with study participation
*Exclusion criteria:*	· Severe medical conditions (metastases, cognitive impairments) · Severe psychiatric disorders (psychotic disorder, risk of self-harm /suicide, acute substance related disorder, personality disorders except for cluster C, organic mental disorder) · Concurrent psychotherapeutic treatment

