### Objectives

The main purpose of the ongoing trial is to determine the efficacy of the manualized STPP regarding remission of depression in breast cancer patients. Secondary outcomes refer to changes of quality of life and to the effect of subtype of depression on treatment outcome.

Based on non-responder analyses we intend to answer the question, which patients do not accept psychotherapeutic treatment for what reason and which characteristics (e.g. age, marital, social status, illness variables, type of depression) have an impact on treatment outcome?

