**Figure 1 F1:**
[figure not shown]
**Study design and patient recruitment (N = projected numbers).** Notes: a) Questionnaires filled out by the patients; b) Structured Clinical Interview for DSM-IV applied by trained interviewers; c) HADS score for depression ≥ 8 & SCID-I diagnosis estimated in 20% of the cases (N = 240 eligible patients) of whom 75% are expected to be consent with randomization; d) Expected completer 80%, e) Expected completer 70%.

We plan to recruit N = 90 participants per group. To ensure adequate randomization stratified for the center, the random assignment to STPP or TAU was performed separately by research staff from the responsible center (not engaged in the project) using a computer-generated
[25] number series of random length (contained within closed, opaque envelopes.).

STPP entails five pre-treatment and up to 20 therapeutic sessions over a period of six months. In each center a close collaboration was established with about 10 psychodynamic psychotherapists in private practice who were trained according to the manual and supervised on a regular basis. Intensive training (at least 2 x 2 hours) is performed in a group format by the respective local study center prior to entering the first patient. Supervision is performed on a monthly basis (3 hours) in the group. In order to assure adherence to the manual, it is recommended that therapists present patients in supervision three times (initial formulation of CCRT based on relationship episode interview, middle and termination phase of treatment).

Patients randomized to the TAU condition are not offered STPP, but obtain written information on local cancer counseling centers and get written information on psychodiagnostic findings to their general practitioner who may then initiate antidepressant treatment (‘as usual’). Utilization of medical, psychotherapeutic and psychopharmacological treatment is documented throughout the study.

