### Statistical analyses

The primary endpoint remission after the treatment phase will be analyzed by a logistic regression with fixed effects for treatment and center and the baseline HADS value as covariate. The primary population for analysis will be the population intended to treat (ITT) consisting of all randomized patients. Dropouts will be regarded as non-remitters. For sensitivity the analysis will be repeated for the completers of treatment population. Additionally, the single components (HADS improvement of ≥2 points, remission according to SCID) will be analyzed separately by the same analysis model as the combined endpoint.

Secondary analyses include the remissions at the end of the follow-up. Remissions at the end of the follow-up will be evaluated accordingly. The quality of life (QoL) questionnaires will be analyzed by an analysis of covariance (ANCOVA) model with fixed effects for treatment and center and the baseline values (HADS depression score & Qol) as covariates. It is expected that the QoL questionnaires will not be linear across the study. Therefore QoL questionnaires after the follow-up will be evaluated by a linear model with fixed effects for treatment, center and time. There will be an indicator variable for the post treatment visit. The HADS value at baseline will serve as a covariate. For QoL data the observed values will be analyzed. However, if the number of missing data is more than 10%, the data will be evaluated after multiple imputation of the data by a Markov chain Monte Carlo (MCMC) method. The impact of moderator variables (age, marital, social status, illness variables, type of depression) is tested in regression analyses.

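### The primary model leaves out the SCID entry diagnosis, so some precision is forgone and a chance imbalance in diagnosis would stay in the primary estimate; the stated sample size, power and type I error stand

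*Protocol article*

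**What the plan says.** - **Eligibility** (Participants, Table 1): "Depressive disorder according to SCID-I (ICD-10 diagnoses: depressive episode F32.-, recurrent depressive episode F33.-; Dysthymia F34.1, adjustment disorder F43.21". All these groups must also meet "Depression score (HADS ≥ 8".
- **Endpoint** (Outcome): a HADS depression fall of at least 2 points together with remission of the SCID-I diagnosis at treatment termination.
- **Randomisation** (Study design, text under Figure 1): "To ensure adequate randomization stratified for the center". No other stratification factor is named.
- **Primary model** (Statistical analyses): "logistic regression with fixed effects for treatment and center and the baseline HADS value as covariate", in all randomised patients, with dropouts counted as non-remitters.
- **Where type of depression appears**: Objectives names "the effect of subtype of depression on treatment outcome" as a secondary matter, and Statistical analyses adds "The impact of moderator variables (age, marital, social status, illness variables, type of depression) is tested in regression analyses". The article does not say whether this type is the SCID diagnosis or the dependent versus self-critical distinction (DEQ) of hypothesis 3.

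**The concern.** The endpoint is defined on the diagnosis with which the patient enters. A reaction to a stressor, an episode and a chronic disorder can be expected to differ in how often they have resolved after six months, so entry diagnosis is a likely predictor of the primary outcome. It is recorded before randomisation, so adjusting for it needs no new data. The article states the covariate set of the primary model outright, so this is a choice the plan has made and not a detail left to a later document.

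Two things are at stake. One is the precision that a prognostic covariate would add. The other is how credible the single observed estimate would be if the arms happened to differ in diagnosis. The moderator regressions do not supply this, because they leave the primary estimate unadjusted. Baseline HADS covers severity, but not whether the condition is reactive, episodic or chronic.

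**Working it through.** **Inputs from the article:** remission 25% (TAU) and 50% (STPP), two-tailed test, power 0.80, dropout 30% and 20%, N = 156 required, 90 per arm planned. Alpha is not stated; 0.05 is assumed because it reproduces N. The diagnosis mix and its prognostic strength are not given, so every figure that uses them is an assumption.

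**1. The plan's own figure.** n per arm = [1.96·√(2·0.375·0.625) + 0.8416·√(0.25·0.75 + 0.50·0.50)]² / 0.25² = (1.342 + 0.557)² / 0.0625 ≈ 57.7, so 58. Inflating for dropout, 58/0.70 → 83 and 58/0.80 → 73, and 83 + 73 = 156, as stated. The 25% and 50% are rates over the whole mixed population, so leaving diagnosis out takes nothing from the planned 0.80. With dropouts as non-remitters the rates become 0.25·0.70 = 17.5% and 0.50·0.80 = 40%, and power at 90 per arm is 0.92.

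**2. Chance imbalance at 90 per arm.** The SD of the between-arm difference in a diagnosis share s is √(2·s(1−s)/90).
- s = 0.30: SD = 0.068, and P(difference above 10 points) ≈ 0.14.
- s = 0.50: SD = 0.075, and the same probability ≈ 0.18.

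Simulation gave 0.14-0.18. If remission differed by 35 points between diagnoses (assumed), a 10-point imbalance would move the observed arm difference by 0.10·35 = 3.5 points. The standard error of that difference is √[(0.25·0.75 + 0.50·0.50)/90] ≈ 7 points.

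**3. Type I error.** In simulations with 90 per arm and no treatment effect, the rejection rate without diagnosis in the model was 0.047-0.056, the same as with it within simulation error.

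**4. Power with and without diagnosis, 90 per arm** (centre and baseline HADS in neither model).

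| Assumption | Without | With |
|---|---|---|
| Two diagnosis groups, share 30-50%, prognostic OR 1.5-5, 25% vs 50% overall | 0.94-0.95 | 0.94-0.96 |
| Three groups, planned 25-point difference | 0.91-0.95 | 0.95-0.98 |
| Three groups, treatment OR 3.0 within diagnosis | 0.85; 0.91; 0.75 | 0.92; 0.94; 0.89 |
| Three groups, treatment OR 2.3 within diagnosis | 0.59; 0.72; 0.53 | 0.68; 0.75; 0.65 |

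The gain is about 0-6 points in the first two rows (about 0-4 with dropouts as non-remitters) and 3-14 points in the last two.

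**5. Why the last two rows are lower.** They assume a smaller effect than the plan does. Take 50% episodes, 20% dysthymia and 30% adjustment disorder, with TAU remission of 20%, 10% and 70%. TAU overall is 0.5·20 + 0.2·10 + 0.3·70 = 33%. An OR of 2.3 within each group gives 36.5%, 20.4% and 84.3%, or 47.6% overall, a difference of 14.6 points. An OR of 3.0 gives 42.9%, 25% and 87.5%, or 52.7% overall, a difference of 19.7 points. Neither is the planned 25.

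**The case against.** The strongest case against is that this is a preference among valid models. Nothing in the article is contradicted, the planned test is valid, and at the planned effect power at 90 per arm is already above 0.90. Baseline HADS may absorb part of what diagnosis would explain, and the simulations above leave HADS out. Diagnosis mix and prognostic strength are wholly assumed. With few dysthymia patients a three-level factor may be unstable. All of this stands, and it limits the size of the point. It does not remove it, since the covariate costs almost nothing and is tied directly to the endpoint.

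Several stronger readings are tempting, and the article does not support them.
- **The primary odds ratio is biased.** Chance imbalance under randomisation is not bias. Its variability is already in the standard error, and type I error is nominal (step 3).
- **The trial is underpowered.** Powers of 0.53-0.72 need a treatment OR of 2.3, which is not the plan's effect. Suppose instead that 20% of patients have adjustment disorder and remit at 60% in both arms. The rates are then 0.8·25 + 0.2·60 = 32% and 0.8·50 + 0.2·60 = 52%, with power 0.59 at 58 per arm. Under the actual primary rule they are 32·0.70 = 22.4% and 52·0.80 = 41.6% at 90 per arm, with power 0.79. A covariate would not cure such dilution in any case.
- **The planning figures exclude adjustment disorder.** "The combined prevalence of major, minor depression and dysthymia in cancer patients was estimated at 22"% is background epidemiology. Recruitment rests on the 20% in the Figure 1 note, under the trial's own criteria. The 25% and 50% were set pragmatically for cancer patients with comorbid depressive disorders, a heading under which Table 1 itself lists adjustment disorder. That they leave it out is inference.
- **Diagnosis is already handled as a moderator.** This is uncertain, because the type of depression meant is not defined, and a moderator analysis would not adjust the primary estimate.

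**Conclusion.** The point holds as a recommendation on the primary model. The plan collects a likely strong predictor of its own endpoint before randomisation and does not use it in the primary analysis. N = 156, power 0.80 and type I error are not in question. The loss is forgone precision: about 0-6 points of power at the planned 25-point difference, and up to about 10-14 points only if the effect is smaller and diagnosis is very strongly prognostic. In addition, an imbalance above 10 points, with a chance of roughly 14-18%, would go unadjusted in the primary estimate. These figures rest on an assumed diagnosis share of 30-50%, assumed remission rates by diagnosis, alpha 0.05, and simulations without centre and baseline HADS.

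**What to change.** In Statistical analyses, before unblinding:
1. Add SCID entry diagnosis (depressive episode F32/F33; dysthymia F34.1; adjustment disorder F43.21) as a fixed effect in the primary logistic model and in its follow-up and single-component versions.
2. State a rule for merging to adjustment disorder versus other if a category is too sparse, judged on counts pooled over the arms.
3. State that the type of depression in the moderator analysis includes the SCID diagnosis.
4. Add a supportive analysis of the primary endpoint without F43.21 patients, so that a reader can see how far the result depends on them. It has fewer patients and should not replace the primary analysis.

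The cost is wording and one or two extra parameters. Eligibility, randomisation and sample size stay as they are. The change has to precede unblinding, because an adjustment chosen afterwards would be post hoc.

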### Intervention

The intervention group is offered a manualized STPP adapting the approach of Luborsky et al.
[8,14] to the specific needs of depressed breast cancer patients
[12]. Following the concept of the Core Conflict Relationship Theme (CCRT), depression is conceptualized in the context of intrapsychic and interpersonal conflicts. The CCRT is the treatment focus characterizing a maladaptive relationship pattern consisting of a wish, the response of the other and of the self. Five pre-treatment sessions include history taking (also the basis for formal application to the health insurance) and eliciting relationship episodes in the relationship interview to formulate the CCRT. The treatment agreement is established in one of the sessions. The therapist shares the CCRT with the patient, informs him about depression and about the treatment rationale in order to engage him in treatment. In the *initial* treatment phase (sessions 1–6), the therapist encourages building a positive alliance and links depressive symptoms to the CCRT. In the *middle* phase (sessions 7 to 12), the therapist refines the CCRT based on further relationship episodes from past, ongoing relationships and the relationship to the therapist. The vulnerability to depression is reduced when its dynamic can be understood from different points of view. In the *termination phase* (13 to 18) the therapist focuses on the issues of separation and the patient’s ability to transfer the tools acquired in treatment to daily life. *Booster sessions* (19, 20) help to consolidate treatment progress. Treatment principles explicitly specified consider both the depressed state (e.g. dealing with helplessness/ hopelessness, anger, suicidality, negative attribution style) and the chronic and life-threatening disease (e.g. realistic treatment goals, here and now perspective, resource orientation). Psychodynamic therapists are certified or advanced trainees with psycho-oncological experience. They are trained in the manualized treatment during workshops before starting treatments and are regularly supervised during the treatments. For the supervision, each patient receiving the STPP intervention is presented at three time points (formulation of the CCRT after the relationship interview, in the middle phase of STPP and in the termination phase of STPP). Supervision is free of charge for the participating psychotherapists. Each session is videotaped. For the evaluation of treatment adherence and competence cf. assessment.

### Assessments

At baseline, patients fill out the HADS
[15] in the German version (HADS-D)
[16], a standardized questionnaire devised for the assessment of depression and anxiety in somatic illness with 14 items. Quality of life is assessed by the generic 30-item questionnaire of the European Organization for Research and Treatment of Cancer Quality of Life Questionnaire - Core 30 (EORTC QLQ-C30)
[17] differentiating a global health status, functioning (physical, role, emotional, cognitive, social) and symptoms (e.g. fatigue, nausea and vomiting, pain etc.). Furthermore, the breast cancer specific quality of life module (EORTC QLQ-BR23)
[18] which consists of functional scales (body image, sexual functioning, sexual enjoyment, future perspective) and symptom scales (system therapy side effects, breast symptoms, arm symptoms and upset by hair loss) is used. The validated German version of the Depressive Experience Questionnaire (DEQ)
[19] is used to identify prognostically relevant personality dimensions of dependency (loneliness, helplessness, fear of rejection), perfectionism or self-criticism (worthlessness, failure, guilt, critical self-monitoring) and self-efficacy (ambitious, competitive and self-reliant stance). The Multidimensional Fatigue Inventory (MFI)
[20] is a 20 item self-report instrument covering the dimensions general fatigue, physical fatigue, reduced activity, reduced motivation and mental fatigue. The German version
[21] of the Helping Alliance Questionnaire (HAQ)
[14] an 11-item rating scale for assessing perceptions of the therapeutic relationship and process is filled out by the patient and therapist at the end of psychotherapy. The Structured Clinical Interview for DSM-IV
[22] is used for standardized (‘gold standard’) assessment of axis I diagnoses. The PACS-SE (Penn Adherence/Competence Scale) with 45 Items
[23] is used in the German version
[24] for independent assessment of therapist adherence and competence based on randomly selected videotaped therapy sessions.

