### Hypotheses

Primary outcome:

1) Higher rate of remission in STPP vs. ‘treatment as usual’ (TAU) at treatment termination.

Secondary outcomes:

2) Six months after the end of treatment lower rate of depression and a higher quality of life among the STPP group compared to TAU.

3) Better outcome in dependent/anaclitic vs. self-critical/ perfectionistic depression (DEQ).

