### Outcome

Remission of depression is defined by reduction of the HADS depression-score (at least by 2 points) and remission of depression (SCID-I-diagnosis) at treatment termination.

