## Discussion

This is the first trial to determine the efficacy of a manualized STPP regarding remission of depression in breast cancer patients. Secondary outcomes refer to changes of quality of life and to the effect of subtype of depression on treatment outcome. Unlike previous studies we required a diagnosis of depression for study entry and we used remission of depression as a clinically relevant outcome criterion.

As we wish to contribute to evidence-based psycho-oncological care we chose as a control condition treatment as usual. We are aware that quality of care for the individual patient in the control condition may vary. However, we actually perform an augmented TAU condition by referring patients to a collaborating cancer counseling center which may provide individual counseling or further referral. We also take great care to send written and detailed findings on the comorbid depression diagnosis to the general practitioner of all the patients (IG and CG) who have given their written consent to do so. We make sure that we carefully assess the actual health care utilization by all patients during both follow-ups.

As we planned to provide an intervention for acute care, we recruit patients who are still in active treatment (chemotherapy, radiotherapy). Recruiting in the major local clinics we make sure that we could assess and contact the breast cancer patients with comorbid depression. We are aware, however, that a substantial proportion of patients would refuse study participation feeling strongly burdened by ongoing treatment. Based on non-responder analyses we intend to answer the question, which patients do not accept psychotherapeutic treatment for what reason
[31]. Including the important dimensions of therapeutic alliance and personality dimensions shaping the experience and expression of depression we also ascertain who benefits most from treatment.

Previous studies of STPP adapting the approach of Luborsky et al.
[8,14] found no sex differences regarding treatment response
[9]. Supportive-expressive psychotherapy has proven a robust model of short-term treatment for a diverse range of mental disorders. We therefore anticipate that it will be possible to transfer the treatment manual also to other kinds of cancer with comorbid depression less frequently studied - particularly in men.

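### The only stated alliance (HAQ) rating coincides with the primary outcome, so for remission at termination it can show a concurrent association but not prediction

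*Protocol article*

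**What the plan says.** Three places in the protocol article give the therapeutic relationship a predictive or causal role. The Background part of the Abstract announces "predictors of outcome by personality and quality of the therapeutic relationship". The Background section states that "an additional issue of our trial is to determine the effects of personality and quality of the therapeutic relationship on treatment outcome". The Discussion adds: "Including the important dimensions of therapeutic alliance and personality dimensions shaping the experience and expression of depression we also ascertain who benefits most from treatment".

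Under Assessments, the instrument for this is the HAQ, described as "an 11-item rating scale for assessing perceptions of the therapeutic relationship and process". It "is filled out by the patient and therapist at the end of psychotherapy". The text gives no earlier rating.

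The Outcome section defines the primary endpoint as a fall of at least 2 points on the HADS depression score together with "remission of depression (SCID-I-diagnosis) at treatment termination". The Abstract places assessments before treatment, at 6 months (treatment termination) and at 12 months.

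The alliance is not named under Objectives or Hypotheses, nor among the moderator variables listed under Statistical analyses.

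**The concern.** A predictor has to be fixed before the outcome it is meant to predict. Here patient and therapist rate the relationship when therapy ends, having lived through whatever improvement has or has not occurred, and remission is assessed at the same stage. A patient who feels better may rate the relationship and the process more favourably for that reason alone. A positive association at termination would then be read as alliance producing remission when the arrow may run the other way.

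Patients who leave therapy early may also have no rating. Statistical analyses counts dropouts as non-remitters, so any ratings lost this way would come from one outcome group only.

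At stake is how one additional aim can be interpreted. The timing is set at data collection, so no later analysis can supply an early rating that was never taken.

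**Working it through.** **Order of measurement, from the text**

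| Item | When | Where stated |
|---|---|---|
| Baseline HADS | before treatment | Assessments |
| Alliance-building phase | sessions 1 to 6 | Intervention |
| HAQ, patient and therapist | end of psychotherapy | Assessments |
| Primary remission | treatment termination, 6 months | Abstract, Outcome |
| Follow-up remission and quality of life | 12 months | Abstract, Hypotheses, Statistical analyses |

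The HAQ and primary remission share a row in time, so there is no temporal order between them. Between the HAQ and the 12-month outcomes there is. The blinded SCID assessors do not remove the problem at termination, because the possible distortion enters through the HAQ rating and not through the interview.

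**Patients concerned**

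The article gives no figure for the alliance analysis, so there is none to reproduce. The HAQ concerns the therapy, so it applies to the STPP arm.
- Planned STPP patients: 90 (Study design).
- Expected STPP dropout: 20% (Sample size calculation), so 0.20 × 90 = 18.
- Expected completers: 90 − 18 = 72.

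**Illustration under assumed colouring**

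Suppose the alliance has no effect on remission, but the end rating correlates r with outcome because improvement colours it. The documents give no value for r; 0.2 to 0.4 is assumed. With a two-sided 5% test (also assumed) and the Fisher z approximation, the chance of a significant association is Φ(atanh(r) × √(n − 3) − 1.96), with n = 72 and √69 = 8.307.
- r = 0.2: 0.2027 × 8.307 − 1.96 = −0.276, Φ = 0.39.
- r = 0.3: 0.3095 × 8.307 − 1.96 = 0.611, Φ = 0.73.
- r = 0.4: 0.4236 × 8.307 − 1.96 = 1.559, Φ = 0.94.

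Fisher z treats both variables as continuous, whereas remission is binary. A simulation respecting that (72 completers, 50% remission, t test of the rating by remission status, 4,000 runs) assumed that remitters rate the alliance higher by 0.3, 0.5 or 0.8 SD. It gave a significant result in about 23%, 55% and 91% of runs, and 5% with no shift.

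The two calculations agree. With an even split, a shift d corresponds to r = d/√(d² + 4), that is 0.15, 0.24 and 0.37. The formula then gives 0.24, 0.54 and 0.90.

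These are not false-positive rates in the usual sense. Under the assumption an association exists; what fails is its reading as prediction.

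**The case against.** The strongest reply is that the aim is not lost. The article speaks of outcome in general and does not tie the alliance to the 6-month endpoint. It plans 12-month remission and quality of life, and the HAQ precedes both. This stands: a reader might infer that the predictor question cannot be answered at all, and the documents do not support that. It can be addressed for 12-month outcomes, although the rating may still carry the 6-month result, hence the adjustment for 6-month status.

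Further objections stand in part.
- **Figure 1.** It is said to show time points and measures, and it is not available. That the HAQ is given only once rests on the sentence in Assessments, which is explicit.
- **Early leavers.** A reader might infer that 18 of 90 STPP patients will have no rating. The text does not say so: the end of psychotherapy can include an early end. They may lack a rating; 18 is only the expected dropout.
- **Knowledge of the result.** Nothing says that patient or therapist knows the SCID finding when completing the HAQ. The argument needs only that they perceive improvement.
- **Weight.** The article itself calls the topic an additional issue, and no numbered hypothesis names the alliance.

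A reader might also extend the point to personality, where the hypothesis reads "Better outcome in dependent/anaclitic vs. self-critical/ perfectionistic depression (DEQ". That does not follow. The DEQ is described among the measures in the paragraph that opens with baseline, its dimensions are presented as prognostic, and the form of the regression model is commonly left to the analysis plan.

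**Conclusion.** The point holds for remission at termination. On the stated timing, the alliance analysis for that outcome can yield only a concurrent association in the STPP arm, open to reverse causation. It does not hold for the 12-month outcomes.

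The size cannot be taken from the documents. The percentages are illustrative and depend on assumed correlations or shifts, 72 completers and a two-sided 5% level. They show that even moderate colouring of the ratings could readily produce a significant association.

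The conclusion rests on the Assessments text being complete on HAQ timing; an earlier rating in Figure 1 would resolve it. Severity is minor: an additional aim is affected, the primary comparison of STPP with TAU is not, and the improvement is cheap.

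**What to change.** 1. Add one HAQ by patient and therapist in the initial phase (sessions 1 to 6). Use it as the predictor of remission at termination, adjusted for baseline HADS.
2. Report the end-of-therapy HAQ as a correlate of remission at termination. Use it as a predictor only for 12-month outcomes, adjusted for 6-month depression status.
3. Word the aim in the Abstract, Background and Discussion to match.

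The cost is one more 11-item form per patient and per therapist, with no added visit and no change to randomisation, treatment or the primary endpoint. Patients already past session 6 in this ongoing trial will lack the early rating, so the number who have it should be reported. An early rating restores temporal order but does not by itself prove causation, since improvement before it is taken could still influence it. The second and third steps cost nothing and are worth making even if the extra form cannot be introduced.
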